### Research personnel

2.7

Experienced physicians will be responsible for recruiting and evaluating the participates in this trial. Postgraduates in gastroenterology will be trained by the principal investigator before participating in this trial. They will dispatch drugs, fill in case report forms (CRFs), and record detailed reasons for the patient's withdrawal from the trial.

### Recruitment and Encouragement

2.8

Six trained investigators and their postgraduates will perform this procedure together. A total 240 patients will be recruited from out-patient and ward of the 6 clinic centers mentioned above, from May 2019 until December 2021. Before the enrollment, all the patients will receive a comprehensive view of informed consent, including objective, therapeutic interventions, scheduling, trial benefits, and possible risks of this trial. Only after signing a written informed consent, patients could be enrolled in it. Meanwhile, to guarantee the completeness of this trial, we will handsel drugs to the patients who have participated it completely.

### Collection of biological specimens

2.9

The patient's stool, blood and colorectal mucosa samples will be collected before and after intervention, and clearly marked according to the unified format. A designated investigator will centrifuge blood samples in the laboratory. Then, the samples were transferred in frozen pipe and stored at −80°C for preservation in the biological sample bank of School of Life Sciences, Beijing University of Chinese Medicine. Consents and other documents like the collection and usage of participant data and biological specimens could be inquired from the registry web or the corresponding author.

## Interventions

3

### Medications

3.1

HEC (HEC, 0.4 g/capsule, supplied by Anhui Joyfar Pharmaceutical, Anhui, China.), EMT (0.5 g/tablet, supplied by LOSAN Pharma GmbH, Neuenburg, Germany),and placebos prepared identical in size, color, shape, taste, smell, and consistency to the 2 above drugs, respectively (supplied by Anhui Joyfar Pharmaceutical, Anhui, China). HEC is a combination of Polygonum cillinerve Ohwi (Zhushaqi), Polygonum Cuspidate (Huzhang), Oldenlandia diffusa (Baihuasheshecao), Sonchus Brachyotus DC (Beibai’jiang), Limonium bicolor (Er'sebuxuecao), Radix Sanguisorbae Preparata Nigra (Diyutan), Bletilla striata (Baiji) and Radix Glycyrrhizae (Gancao). In this trial, an administrator was assigned to manage the drugs, including drug storage, distribution, and recycling independently and kept detailed records.

### Intervention plan

3.2

Both 2 groups will be treated with drugs for 8 weeks continuously, and the administration method of drugs has been designed as described in Table 1.

**Table 1 T1:**
[figure not shown]
Administration methods in the experimental and control groups.

### Follow-up

3.3

Each patient was provided with a participant diary card to record diary signs and symptoms of diarrhea, mucilage or blood–pus stools, abdominal pain, and tenesmus. Patients will be interviewed every 2 weeks after enrollment in the trial, while they should return the remaining drugs and packages, and receive the drugs they need to take for the next 2 weeks. Assessment of study endpoints and duration of follow-up was shown in Figure 2.

**Figure 2 F2:**
[figure not shown]
Follow-up protocol schedule chart during the trial. UC = ulcerative colitis, TCM = traditional Chinese medicine.

### Outcomes

3.4

Primary therapeutic outcome: the rate of clinical efficacy and clinical remission at 8 weeks of treatment (last survey point) according to the modified Mayo score (Table 2). Clinical efficacy was defined as a decrease of at least 30% from the baseline and a decrease ≥3 points, with an accompanying decrease in the subscore for bloody stools ≥1 point or absolute bloody stools subscore of 0 to 1. Clinical efficacy rate = effective number / total number of the group ×100%. Clinical remission was defined as a score ≤2, with no individual subscore with a value greater than 1. Clinical remission rate = remission number / total number of the group ×100%.

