### Number of Samples

2.3

Number of Samples was determined based on the calculation of noninferiority trial design. The efficacy rates of EMT ranges from 65% to 71%,^[12,13]^ and the average rate is about 68%. Our previous study found that the efficacy rates of HEC is 83.11% in treating MAUC. The sample size was calculated by the following formula: 

*U*α, *U*β is the corresponding *U* value of α, β. When α equaling to 0.05, β equaling to 0.1, *U*α (0.05) is 1.645, *U*β (0.2) is 0.842. *P*_1_ and *P*_2_ represent the efficacy rates of HEC and EMT. *P* equals to (*P*_1_ + *P*_2_) /2 × 100%. The certainty was set at 80%, considering 20% of sample lose. The sample number was set to 120 for each group, 240 in total, and 40 samples in each center.

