### Data analysis

3.7

Data analysis will be performed by professional statisticians and the main researchers using SPSS 22.0. Statistical analysis included the actual number of subjects selected, cases of shedding and rejection, demography and other baseline characteristics, patient compliance, efficacy and safety analysis. We used frequency tables or percentages for categorical variables, and mean ± standard deviation for continuous variables to describe the characteristics of patients in both groups. Categorical data will be analyzed by chi-square test or Fisher exact test to compare the differences between the 2 groups, while quantitative data with normal distribution will be analyzed by *t* test. If the data does not conform to the normal distribution or the uniformity of variance, Wilcoxon rank sum test or Wilcoxon signed test will be used to analyze them to compare the two groups. A two-sided *P-*value <.05 will be set as the significant level.

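### Two rates are called primary without an order or success rule, one general 0.05 level applies, and only clinical efficacy was sized

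*Protocol article*

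**What the plan says.** Section 3.4 Outcomes states: "Primary therapeutic outcome: the rate of clinical efficacy and clinical remission at 8 weeks of treatment (last survey point"), by the modified Mayo score. The abstract repeats the pair. Each rate has its own definition, numerator and formula: "Clinical efficacy rate = effective number / total number of the group ×100"% and "Clinical remission rate = remission number / total number of the group ×100"%. They are therefore two proportions and not one composite.

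Section 3.7 Data analysis compares categorical data by chi-square or Fisher exact test and gives one rule for all tests, a two-sided P "value <.05 will be set as the significant level". It gives no order and no split of alpha.

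Section 2.3 Number of Samples bases the calculation on P1 and P2, which "represent the efficacy rates of HEC and EMT". The planning values are 83.11% for HEC, and for EMT a range of 65% to 71%, "and the average rate is about 68"%. No remission rate appears anywhere in the article.

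**The concern.** With two primary rates, the meaning of a positive trial depends on a rule that the article does not state. If either rate suffices, two chances at 0.05 carry more than a 5% risk of a false significant result. If both are needed, the error rate is safe, but power is lower than for a single endpoint. The sample size was derived for one endpoint and allows for neither case.

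The two rates can also disagree. Inclusion requires a modified Mayo score of 3 to 5 (section 2.5). Efficacy needs a fall of at least 3 points, and remission needs a final score of 2 or less with no subscore above 1. At some baseline scores a patient can meet one definition and fail the other, so a split result is possible. Without a rule fixed beforehand, the choice of which rate to headline could be made after the results are known.

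**Working it through.** **1. Reproduce the planned sample size.** Inputs from section 2.3: P1 = 0.8311, P2 = 0.68, Uα = 1.645, Uβ = 0.842, 20% loss. The text has "When α equaling to 0.05, β equaling to 0.1", but the Uβ value used is labelled 0.2, and the section also says "The certainty was set at 80%, considering 20% of sample lose". Power is therefore taken as 80%.

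- P = (0.8311 + 0.68)/2 = 0.75555, so 2P(1−P) = 0.3694.
- (1.645 + 0.842)² = 6.185 and (0.8311 − 0.68)² = 0.02283.
- n = 0.3694 × 6.185/0.02283 = 100.07 per group.
- 100.07 × 1.2 = 120.1, which is the stated 120.

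The formula is not legible in the article, but this standard one returns the stated figure from the efficacy rates alone. It leaves no allowance for a second primary rate.

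**2. Error rate if either rate suffices.** Treat the two test statistics as bivariate normal with correlation ρ. The article gives no ρ, so a range is shown.

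- At least one false significant result, two-sided: 1 − P(|Z1| < 1.96, |Z2| < 1.96). At ρ = 0 this is 1 − 0.95² = 9.75%.
- At least one false claim in favour of HEC: 1 − P(Z1 < 1.96, Z2 < 1.96). At ρ = 0 this is 1 − 0.975² = 4.94%. The nominal value is 2.5%, half of the two-sided 0.05.

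**3. Power if both must succeed.** Each rate is assumed to have 80% power at one-sided 0.05, the convention of section 2.3. Joint power is the bivariate normal probability P(Z1 < 0.842, Z2 < 0.842). At ρ = 0 this is 0.8² = 64%.

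| Assumed ρ | Either: any false significant result | Either: false claim for HEC | Both: joint power |
|---|---|---|---|
| 0 | 9.75% | 4.94% | 64.0% |
| 0.5 | 9.07% | 4.54% | 68.7% |
| 0.8 | 7.81% | 3.90% | 72.9% |
| 0.9 | 7.04% | 3.52% | 75.0% |
| 0.95 | 6.46% | 3.23% | 76.5% |

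**4. Can an alpha split repair this at the present size?** Splitting 0.05 equally restores control (at most 4.94%). With the formula of step 1 and one-sided 0.025, n = 0.3694 × (1.96 + 0.842)²/0.02283 = 127 evaluable per group, or 152 after ×1.2. With 100 evaluable per group, power for efficacy falls from 80% to about 70%.

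**5. Where the two definitions part.**

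- Baseline 3 or 4: a fall of at least 3 leaves a score of 0 or 1, so efficacy implies remission. A patient who ends at 2 with no subscore above 1 is in remission but is an efficacy failure.
- Baseline 5: both need a final score of 2 or less. Remission implies efficacy, because every remaining subscore, bloody stools included, is at most 1. The reverse fails if the 2 remaining points lie in one subscore.

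The rates overlap heavily but are not interchangeable.

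**The case against.** The strongest reply is that only a condensed article is at hand, and that endpoint order and multiplicity are often settled in the full protocol or analysis plan. A plan that tests efficacy first would keep the present size and control the error rate. That order is even suggested here, since efficacy is listed first and is the only rate sized. This stands in part: an efficacy-led reading loses nothing, and it is the basis of the fix. But the article itself fixes two primary rates without ranking them, together with a sample size built on one. Choosing the primary endpoint and sizing the trial for it are protocol decisions, and a later alpha split or both-must-succeed rule could not recover power at N = 240.

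A reader might infer three stronger things that the document does not support:

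- **That the trial has adopted an either-wins rule at 0.05 each.** It has not. The 0.05 level is stated once for all tests, and joining the rates by a simple conjunction can equally mean that both are required, which inflates nothing.
- **That the risk of falsely favouring HEC is 7% to 9.75%.** Those two-sided figures also count significant results in favour of mesalazine. The risk of a false claim for HEC is at most 4.94%. That exceeds the nominal 2.5%, a level derived here and not printed in the article, but not the one-sided 5% implied by Uα = 1.645.
- **That joint power is known to be 64% to 76%.** Without a remission planning rate, power for remission cannot be calculated. The range also uses the one-sided tests of section 2.3, while section 3.7 specifies a two-sided level, under which power would be lower.

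How often the two definitions would classify patients differently is likewise unknown.

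**Conclusion.** The point holds as an unresolved success rule. Two separately defined rates are primary and unranked, one general level applies, and the stated 120 per group follows from efficacy alone. Read one way, the trial exceeds its nominal error rate; read the other way, it falls short of its stated 80% power. The sizes in the table rest on assumed correlations and, for joint power, on an assumed 80% power for remission. Because the two rates overlap heavily, the values at the higher correlations are the more plausible ones. Overlap reduces the problem but does not remove it. The trial should correct this, but the text does not show that an inflated error rate was planned.

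**What to change.** Before unblinding, name clinical efficacy, the rate the trial was sized on, as the single primary endpoint. Make clinical remission the key secondary endpoint, tested at full alpha only if efficacy succeeds (fixed sequence). The familywise error then stays at the chosen level, because remission is never tested after a failure on efficacy, and N = 240 stands as calculated.

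The change takes a sentence or two in sections 3.4 and 3.7, plus the ethics review and registry update that section 2.1 requires for significant modifications. Its scientific cost is the loss of a second independent chance to win: a favourable remission result could not rescue a failed efficacy comparison.

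If the sponsor prefers remission as primary, wording alone is not enough. A remission planning rate must be stated and justified, and the power restated for N = 240.

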**Methods::**

A multi-center, double-blinding, double-dummy, active-controlled, randomized trial will be established. A total of 240 patients in 6 centers with mild active UC (Mayo score is 3–5 points) and TCM syndrome of damp-heat stasis blocking and spleen-qi deficiency will be randomly allocated in the ratio of 1:1 to 2 groups: the experimental group and the control group. The experimental group will receive Hudi enteric-coated capsules (HEC) and enteric-coated mesalazine tablets placebo; the control group will receive enteric-coated mesalazine tablets and HEC placebo. Each group will be treated for 8 weeks. The primary therapeutic outcome: the rate of clinical efficacy and clinical remission at 8 weeks of treatment (last survey point) according to the modified Mayo score. The secondary outcomes: individual symptom score, TCM syndrome score, endoscopic response rate, mucosal healing rate, and quality of life scale score. Outcomes will be assessed at baseline and the end of the trial. Besides, intestinal mucosa, stools and blood biopsies from the mild active UC patients before and after treatment will be collected to reveal the underlying mechanisms.

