### Eligibility criteria

2.5

Diagnostic criteria:

1.The western medicine diagnostic criteria of UC will refer to Chinese consensus on diagnosis and treatment of IBD (Beijing, 2018).^[14]^2.The TCM diagnostic criteria of the damp-heat stasis blocking and spleen-qi deficiency syndrome will refer to the Clinic terminology of traditional Chinese medical diagnosis and Consensus of traditional Chinese medical in diagnosis and treatment of UC.^[15,16]^ Diagnosis of this syndrome including the main and minor symptoms as following:

Main symptoms:

1.Diarrhea, mucus and bloody stools;2.Abdominal pain;3.Tesmus;4.Tired and lazy;

Minor symptoms:

1.burning anus;2.short and dark-color urine;3.dry and bitter in the mouth;4.drowsiness of limbs;5.poor appetite.

Tongue and pulse: red tongue, thick yellow fur with tooth marks on the sides, and smooth pulse.

Confirmation of the syndrome type: 2 main symptoms (required for the first item) plus 2 minor symptoms, which can be diagnosed by referring to the tongue and pulse.

Inclusion criteria:

1.Diagnosed with active UC.2.Defined by modified Mayo score of 3 to 5 points (mild period).^[14]^3.Differentiation of TCM syndrome is damp-heat stasis blocking accompanied with spleen-qi deficiency.4.Age >18 and <65 years.5.Voluntary to participate and providing written informed consents, as required by Good Clinical Practice.

Exclusion criteria:

1.Patients during remission period, moderate or severe period.2.Pregnancy, lactation, or have desire for pregnancy.3.Severe allergy or allergic to mesalazine or any of the ingredients in HEC.4.Have cardiovascular, pulmonary, liver, renal, endocrine, nerve, and hematology diseases. Blood creatinine level, blood alanine transaminase or aspartate aminotransferase level above the upper limit of normal.5.Have serious complications, such as intestinal stenosis, intestinal obstruction, intestinal perforation, multiple intestinal polyps, toxic megacolon or colorectal cancer, etc.6.Mental disorders or other causes which result in inability of proper expression of feelings.7.Have participated in other medical clinical studies in the last 3 months.8.In addition to mesalazine, receiving other treatments for UC.9.Serious and unstable condition requiring emergency treatment.10.Inappropriate to participate in this trial judged by clinical physicians.

Termination and withdrawal criteria:

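### For patients entering at 3 or 4 points, the primary clinical-efficacy rule is stricter than remission, so some remitters are counted as not effective

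*Protocol article*

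**What the plan says.** Eligibility criteria (2.5) admits patients by score: "Defined by modified Mayo score of 3 to 5 points (mild period". The same section excludes "Patients during remission period, moderate or severe period", so nobody enters outside that band. The abstract gives the same range.

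Outcomes (3.4) names the primary outcome as "the rate of clinical efficacy and clinical remission at 8 weeks of treatment (last survey point) according to the modified Mayo score". Two definitions on that score follow:

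- Efficacy sets a rule on the total score: "Clinical efficacy was defined as a decrease of at least 30% from the baseline and a decrease ≥3 points". It also requires a bleeding condition to be met, by a fall of at least 1 point in the bloody-stool item or a final value of 0 or 1 on it.
- Remission: "Clinical remission was defined as a score ≤2, with no individual subscore with a value greater than 1".

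The article gives no separate efficacy rule for mild disease and does not say that a remitter also counts as effective. Number of Samples (2.3) plans on efficacy rates of about 68% for mesalazine and 83.11% for HEC.

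**The concern.** Response is normally the easier target and remission the harder one, so every remitter should also be a responder. A required fall of 3 points leaves little room when patients start at 3, 4 or 5. If the rule is applied as written, the efficacy rate asks for complete clearance from some patients and something close to remission from others, and some patients count as a success on one primary rate and a failure on the other.

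This concerns the primary outcome of a trial declared to be noninferiority. The reported efficacy rate would be hard to interpret beside the remission rate, and the power calculation may rest on rates measured by a different rule.

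**Working it through.** **Inputs.** Baseline total B = 3, 4 or 5 (2.5). Efficacy: fall of at least 30% of B and at least 3 points, plus the bleeding condition (3.4). Remission: final total F of 2 or less, no subscore above 1 (3.4). The score table is not legible in the text available, so whole-number subscores are assumed.

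**Step 1: what each rule demands.** Efficacy needs F ≤ B − 3.

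| Baseline | 3 points as share of baseline | F for efficacy | F for remission |
|---|---|---|---|
| 3 | 3/3 = 100% | 0 | ≤ 2, no subscore above 1 |
| 4 | 3/4 = 75% | ≤ 1 | ≤ 2, no subscore above 1 |
| 5 | 3/5 = 60% | ≤ 2 | ≤ 2, no subscore above 1 |

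The smallest share is 60%, so the 30% condition is always met once the 3-point condition is.

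**Step 2: order of the two rules.**

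- Baseline 3 and 4: an effective patient ends at 0 or 1, so no subscore can exceed 1 and the patient is in remission. The reverse fails for 3 to 1, 3 to 2 and 4 to 2 when no subscore exceeds 1.
- Baseline 5: a remitter has F ≤ 2, hence a fall of at least 3, and a bleeding subscore of at most 1, so is effective. Efficacy is wider only where the final total of 2 comes from a single subscore of 2.

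The bleeding condition can only narrow efficacy, so it cannot restore the order.

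**Step 3: illustration with four items scored 0 to 3 (assumed).** Final states in remission: all zero (1), one item at 1 (4), two items at 1 (6), total 11. Final states that can count as effective: 1 from baseline 3; 1 + 4 = 5 from baseline 4; 11 + 4 = 15 from baseline 5. With three items the order is the same: 1 against 7, 4 against 7, and 10 against 7. These are counts of possible states, not proportions of patients.

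**Step 4: where the planning rates enter.** The sample-size formula is also not legible, so two standard two-proportion forms were tried with the printed values 1.645 and 0.842, P1 = 0.8311, P2 = 0.68 and P = 0.75555.

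- [1.645·√(2P(1−P)) + 0.842·√(P1(1−P1) + P2(1−P2))]² / (P1 − P2)² = 99.02, rounded up to 100; × 1.2 = 120.
- 2P(1−P)(1.645 + 0.842)² / (P1 − P2)² = 100.07, rounded up to 101; × 1.2 = 121.2, so 122.

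The stated 120 per group is reproduced, so it rests on these two rates. The article does not show that either was obtained with the 3.4 definition in patients scoring 3 to 5. The Discussion says the earlier HEC study lacked enteroscopy and could not take the Mayo score as its primary outcome.

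**Step 5: the 30% rule without the 3-point condition.** 30% of 3, 4 and 5 is 0.9, 1.2 and 1.5, so falls of 1, 2 and 2 points are needed, giving F ≤ 2, ≤ 2 and ≤ 3. Every remission then meets efficacy (3 to 2 is 33%, 4 to 2 is 50%, 5 to 2 is 60%), and its bleeding subscore of 0 or 1 satisfies the bleeding condition.

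**The case against.** The rule is explicit and computable, and it is applied identically and under blinding in both arms. A demanding response criterion is a legitimate choice. Any responder rule on a whole-number scale varies in strictness with baseline, and randomisation balances baseline scores in expectation, so the comparison is not biased by this. All of that stands. It rules out a stronger reading that someone might take from the arithmetic: that the efficacy rate does not measure response at all. It measures a strict response that is badly fitted to the entry range.

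Two other inferences also go too far. Efficacy does not always need a near-zero score: from baseline 5 a final score of 2 can qualify. Nor are the planning rates shown to be wrong: how the mesalazine sources defined efficacy cannot be seen, and the Discussion casts doubt only on the HEC figure. The fair statement is that they are not shown to apply.

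It might also be said that the two rates form one composite. That does not help. If either suffices, efficacy adds nothing at baseline 3 and 4; if both are required, remission adds nothing there. Nor is this a detail left to a fuller document, since both definitions are stated in full.

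**Conclusion.** The point holds for patients entering at 3 or 4. There the efficacy rule is strictly harder than remission, and it labels some remitters as not effective. At baseline 5 the order is the usual one and the definitions nearly coincide. The 30% condition has no effect anywhere in the admitted range.

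The result for baseline 3 and 4 needs only whole-number subscores; only the illustrative state counts depend on the number and range of items. The size in patients is unknown, because the shares entering at 3, 4 and 5 are not given. No figure can therefore be put on the shift in the overall efficacy rate or on the loss of power. It should be corrected before unblinding, because a later change to a primary definition would not be credible.

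**What to change.** Amend Outcomes (3.4) with a dated amendment and registry update before unblinding. Two options:

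1. **Redefine efficacy so that every remitter counts as effective**, for example by dropping the 3-point condition and keeping the 30% fall with the bleeding condition. Downsides: a 1-point fall from 3 to 2 counts as success; at baseline 3 and 4 the total-score cut-off equals that of remission, so the two rates differ only where one subscore stays at 2; and a looser response may separate the arms less well, which matters in a noninferiority trial.
2. **Make remission the single primary endpoint** and move efficacy to the secondary outcomes. Downside: the article gives no planning remission rate, so one has to be justified.

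Under either option, Number of Samples (2.3) should say that 68% and 83.11% were not derived for the chosen definition, and should restate the planning assumption and the power that 120 per group then gives. The endpoint can be recalculated from scores already collected, so no new data are needed. The cost is the amendment, the registry entry and possibly a revised sample size.
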